#### **4.7 Data Collection**

The study variables are extracted from an excel data base that contains the clinical records of VL patients. The main exposure variables in 10% of the patient charts will be validated against the records in the excel database.

#### 4.7.1 Study variables

The main exposure variables mentioned below were identified by literature review for predictive factors for mortality and taking into consideration the data routinely collected in the MSFH program.

- Demographics: age (years) , sex (male or female)
- Clinical
  - o On admission:
    - Duration of illness (weeks or months)
    - Presence or absence of weakness, ascites, peripheral edema, bleeding, jaundice, tuberculosis (TB)
    - Spleen size (cm)
    - Body mass Index (BMI) (in kg/m^2)
    - Hemoglobin (g/dl)
- VL history (Primary VL versus VL relapse); VL treatment received (Antimonial based or other)
- HIV status (negative, positive, discordant)
- Antiretroviral (ART) use (yes or no; duration)
- CD4+ T lymphocyte count (cells/ $\mu$ l), most recent result

#### 4.7.2 Measurement of variables

- **HIV status**

HIV testing is done routinely in all VL suspects upon admission, based on rapid diagnostic testing algorithms according to MSFH and national guidelines.

- **VL history (Primary versus Relapse)**

VL is diagnosed according to MSFH and national guidelines. A suspected VL patient is one who presents with prolonged fever (2 weeks or more) with splenomegaly and/or lymphadenopathy and/or wasting AND has lived or travelled to a known visceral leishmaniasis endemic area. Suspected VL patients undergo further diagnostic evaluations.

A primary VL case is defined as a patient that has never been treated for VL and has a positive rK39 rapid diagnostic test (DiaMed-IT-Leish) or a high-titer ( $\geq 1:3200$ ) of a direct agglutination test (DAT) or a borderline DAT titre (1:800–1:1600) and a positive parasitological test (spleen, bone marrow or Lymph node). Aspirates of the spleen, bone marrow or lymph node are stained with Giemsa and examined under a microscope. At the LRTC, DAT is not performed, rK39

negative patients undergo tissue aspiration (spleen, bone marrow or lymph node) and VL is confirmed parasitologically.

A parasitological test refers to microscopic examination for *Leishmania* amastigotes in giemsa stains of tissue aspirates (spleen, bone marrow or Lymph node). The results are logarithmically graded from 0 (0 parasites/1000 fields) to 6 (>100 parasites/field).

A relapse VL case is defined as a patient previously treated for VL with a positive parasitological test (spleen, bone marrow or Lymph node).

Suspected VL patients with negative serological tests or also negative parasitological tests are evaluated for possible differential diagnoses. If no differential diagnoses are found the patients are rescreened for VL one to two weeks later.

### Primary VL diagnostic algorithm in Abdurafi Health centre

[figure not shown]

- **CD4+ T lymphocyte count:** This is measured in cells/ $\mu$ l using FACS counter (BD FACS Calibur flow cytometer, 2009, USA).
- **ART use:** This is defined from the patient's history and/or records from the HIV clinic and/or visual inspection of the drugs.
- **Body Mass Index:** The BMI is calculated with the following formula.

$$\text{BMI} = \frac{\text{Weight (in Kg)}}{\{\text{Height (in m)}\}^2}$$

The weight is measured with a mechanic scale to the nearest 0.5 Kg.

The height is measured with a stadio meter in centimeters to the nearest 0.5 cm.

- **Jaundice:** This is defined by clinical examination revealing a yellowish coloration of the sclera and reported as either present or absent.
- **Duration of illness:** This is defined from the patient's history and reported in weeks or months.
- **Tuberculosis:** This is defined as follows.
  - Absence of TB: Absence of history and signs suggestive of TB suspect or a suspected TB patient with negative sputum smear results and/or normal radiograph findings and/or normal abdominal ultrasound findings.
  - Presence of TB: History and signs suggestive of TB suspect with positive sputum smear results and/or suggestive radiograph findings and/or suggestive abdominal ultrasound findings or diagnosed by a TB expert.
- **Age:** This is defined from the patient's history and measured in years.
- **Haemoglobin:** The haematological analysis is done by a haematology analyser – Beckman Coulter A®T diff, Beckman Coulter Inc., 2003, USA. Haemoglobin is measured in g/dl routinely upon admission.
- **Severe Weakness:** The MSFH operational definitions of “Severe Weakness” are as defined below;
  - State of collapse = score 5  
Definition of collapse in adults/older children: unable to sit up unaided AND cannot drink unaided.  
Definition of collapse in babies: floppy when held in arms AND unable to feed unaided.
  - Severely weak = score 3  
Definition of severe weakness in adults/older children: cannot walk 5 m without assistance.  
Definition of severe weakness in babies: unable to sit upright unaided.
  - Other types of weakness = score 0

At the LRTC, the definition of weakness was based on the clinician's assessment and classified as either present or absent.

- **Ascites:** This is defined by clinical examination and reported as either present or absent.
- **Spleen size at admission:** This is measured in the anterior axillary line from the coastal margin to the tip of the spleen. The measurements are recorded in centimetres.
- **Bleeding:** This is defined by clinical examination and reported as either present or absent.
- **Oedema:** This is defined by clinical examination and reported as either present or

absent.

- **Treatments:** This is the VL treatment regimen used during treatment and will be measured in 2 groups. A treatment regimen containing an antimonial and a treatment regimen without an antimonial.

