### **Possible limitations**

1. The clinical records of critical patients may contain more complete data compared to the rest of the patients thus creating some bias.
2. There will be some missing data however they are few (<1%). Médecins Sans Frontières Holland has multi-country standardized data collection tools (See Annexe 1). Standardized data collection forms were used to collect the data at the Leishmania Research and Treatment Centre.
3. The definition of the variable “weakness” is not based on the Karnofsky performance scale Index or standardised system at both VL treatment sites.

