### 4.2 Population

**Development of the tool:** All patients diagnosed with primary and relapse VL between January 2008 to December 2013.

**External validation of the tool:** All patients diagnosed with primary and relapse VL between January 2011 and December 2012

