#### **4.5 Inclusion Criteria**

In the derivation and external validation cohort, we will include all patients with the outcomes mentioned below.

1. Cured
2. Dead

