## **11. ANNEXES**

### **Annex 1: kala azar treatment card**

[figure not shown]Admission data entered ☐Exit data entered ☐**Kala Azar Treatment Card****Treatment site: Abdurafi**

Name: \_\_\_\_\_ Patient No.: \_\_\_\_\_ Lab No.: \_\_\_\_\_

Admission date: \_\_\_\_\_ Sex: \_\_\_\_\_ (M/F) Age: \_\_\_\_\_ months/years

Current Address: \_\_\_\_\_ Region: \_\_\_\_\_ Woreda: \_\_\_\_\_ Kebele: \_\_\_\_\_

Migrant Worker / Resident / Settler / Other: \_\_\_\_\_

How long at current address: \_\_\_\_\_ years, \_\_\_\_\_ months

Origin (if not resident): \_\_\_\_\_ Region: \_\_\_\_\_ Woreda: \_\_\_\_\_ Kebele: \_\_\_\_\_

Previous Kala Azar treatment: \_\_\_\_\_ (Y/N) Regime: \_\_\_\_\_

Exit date: \_\_\_\_\_ Location: \_\_\_\_\_

Sick for how long: \_\_\_\_\_ weeks/months Weakness: ☐ Collapse / ☐ Severely weak / ☐ Little or no

Weight: \_\_\_\_\_ kg Height: \_\_\_\_\_ cm Z-score (<19 yrs): \_\_\_\_\_ / BMI (≥19 yrs): \_\_\_\_\_

Spleen size: \_\_\_\_\_ cm Liver size: \_\_\_\_\_ cm Lymphadenopathy: \_\_\_\_\_ (Y/N)

Hb: \_\_\_\_\_ g/dl / Clinical anaemia: \_\_\_\_\_ (Y/N)

Pregnancy: \_\_\_\_\_ (Y/N) Jaundice: \_\_\_\_\_ (Y/N) Oedema: \_\_\_\_\_ (Y/N)

| Severity score     |  |
|--------------------|--|
| Age                |  |
| Weakness           |  |
| Nutritional status |  |
| Hb                 |  |
| TOTAL       |  |

Under TB Tx: \_\_\_\_\_ (Y/N) VCT code: \_\_\_\_\_ ART: \_\_\_\_\_ (Y/N) FUCHIA#: \_\_\_\_\_ CD4 count: \_\_\_\_\_

Malaria RDT - Date: \_\_\_\_\_ Result: \_\_\_\_\_ (neg/pos)

IT Leish (rK39) - Date: \_\_\_\_\_ Result: \_\_\_\_\_ (neg/pos)

DAT - Date: \_\_\_\_\_ Result: \_\_\_\_\_ (neg/bl/pos) Titre (well): \_\_\_\_\_ (0-11)

Aspirate - Date: \_\_\_\_\_ Site: ☐ Spleen / ☐ LN / ☐ BM Result: \_\_\_\_\_ (0-6)Diagnosis: ☐ PKA / ☐ Relapse / ☐ PKDL/PKMDL Treatment regimen: \_\_\_\_\_

Initial doses - SSG: \_\_\_\_\_ PM: \_\_\_\_\_ AmBisome (course): \_\_\_\_\_ Miltefosine: \_\_\_\_\_

Ferrous fumarate/Folic acid: \_\_\_\_\_ tablets Folic acid: \_\_\_\_\_ tablets PlumpyNut: \_\_\_\_\_ sachets

Vit A - Date: \_\_\_\_\_ Dose: \_\_\_\_\_ IU Measles vaccination (<16 yrs) - Date: \_\_\_\_\_

History:

\_\_\_\_\_

\_\_\_\_\_

\_\_\_\_\_

\_\_\_\_\_

Temp: \_\_\_\_\_ °C RR: \_\_\_\_\_ /min PR: \_\_\_\_\_ /min BP: \_\_\_\_\_ mmHg

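### Raw BMI is the only nutritional predictor at every age, although the development site's own card uses a Z-score below 19 years

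*Protocol*

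**What the plan says.** Section 4.7.1 lists BMI in kg/m² among the admission variables and names no other measure of nutrition. Section 4.7.2 says "The BMI is calculated with the following formula" and gives weight in kg divided by the square of height in m. Neither section sets an age limit or an age reference.

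The cohort has no age limit. Section 4.2 takes "All patients diagnosed with primary and relapse VL between January 2008 to December 2013", and section 4.5 selects by outcome: "we will include all patients with the outcomes mentioned below", namely cured or dead. The measurement section allows for very young patients, for example "Definition of collapse in babies: floppy when held in arms AND unable to feed unaided".

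The treatment card in Annex 1, from the development site, splits the nutrition field by age. It has "Z-score (<19 yrs") for the young and BMI from 19 years. The severity score printed on the card has an item called "Nutritional status", not BMI. The protocol text never mentions the Z-score and does not say how the two measures relate.

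Section 4.8.2 turns each predictor into a crude likelihood ratio (LHR) and screens it at 2 or above, or 0.5 or below. It then adjusts the ratio by logistic regression, retains predictors at 1.5 or above, or 0.67 or below, and converts the log of the adjusted ratio into integer points.

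**The concern.** BMI in healthy children changes with age and is normally lower than in adults, which is the usual reason to replace it with an age-referenced Z-score. The card follows that convention and the protocol's predictor does not. If raw BMI is categorised in the same way at all ages, a low category collects adults who are wasted together with children who may be normally nourished for their age.

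Two things are at stake. The first is development: mixing two meanings in one category pulls its LHR towards 1 and ties it to age, which is itself a candidate predictor. A real effect of malnutrition could then miss a fixed screening or retention limit. The second is use: the Summary and section 1.2 intend the score to help decide who is treated in hospital or health centre and who is monitored intensively. BMI points derived mainly from adults would be misread in a child.

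**Working it through.** **Step 1. Does the stated definition apply to children?** Section 4.7.1 gives one unit for all patients, section 4.7.2 gives one formula for all patients, and sections 4.2, 4.5 and 4.6 contain no age criterion. Followed as written, the plan gives a child a raw kg/m² value.

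**Step 2. Does the source form agree?** No. Annex 1 uses the Z-score below 19 years and BMI from 19. Section 4.7.1 says that the predictors were chosen with routinely collected data in mind, but below 19 years the routine nutritional measure on the card is the one the protocol leaves out.

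**Step 3. Would BMI be missing below 19 years?** Not on the text. The protocol calculates BMI, and the card has weight and height fields without an age limit.

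**Step 4. How many patients could be affected?** The documents give 1729 patients in the development cohort but not the number under 19. At an assumed share s, the count is s × 1729:

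| Assumed share under 19 | Patients |
|---|---|
| 5% | 86 |
| 10% | 173 |
| 20% | 346 |
| 30% | 519 |

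These are counts of minors, not of errors.

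**Step 5. Can the LHR cross a limit?** This is an illustration with assumed figures. Suppose that, in adults, a low-BMI category holds 40% of deaths and 18% of survivors. The LHR is 0.40/0.18 = 2.22, which passes the crude screen of 2. Let a share s of both deaths and survivors be under 19, and let a fraction f of them fall in the low category regardless of outcome. Then

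LHR = [0.40(1 − s) + f·s] / [0.18(1 − s) + f·s].

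| s | f | Deaths in category | Survivors in category | LHR | Screen at 2 |
|---|---|---|---|---|---|
| 5% | 0.5 | 40.5% | 19.6% | 2.07 | passes |
| 5% | 1 | 43.0% | 22.1% | 1.95 | fails |
| 15% | 0.5 | 41.5% | 22.8% | 1.82 | fails |
| 15% | 1 | 49.0% | 30.3% | 1.62 | fails |

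The illustration is deliberately unfavourable, because it assumes that raw BMI carries no information about death within the under-19s. It shows only that a modest share can matter for a predictor close to the limit.

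**Step 6. Does adjustment for age repair this?** Only in part. The screen in section 4.8.2 uses crude ratios, so a predictor lost there never reaches the adjusted model. In the model, an age term shifts the baseline risk by age. It does not make one BMI category mean the same nutritional state in a child and an adult.

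No figure stated in the protocol is disputed here. The limit of 9 parameters (99/10 = 9.9) reproduces, and the fix does not change it if the combined variable has as many categories as BMI would have had.

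**The case against.** The strongest reply is that the protocol fixes no BMI cut-off. An LHR can be calculated for each level of a variable with several categories, and the categories, even age-specific ones, may be left to a statistical analysis plan that is not shown. This stands against any claim that the protocol imposes a single adult cut-off. It does not remove the point, because the protocol itself names the variable, its unit and its formula. An analysis plan that keeps to them inherits raw BMI, and more categories of raw BMI still have no age reference.

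A reader might infer a stronger fault: that everyone under 19 lacks BMI, in conflict with the statement "There will be some missing data however they are few" (under 1%). The documents do not support this, for the reason in step 3. A reader might also take 86–519 as the number misclassified. That does not follow either: a severely wasted child may be low on both measures, and raw BMI at 18 years is close to its adult meaning.

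Three further replies have weight. Section 4.1 says that most patients are migrant workers, which suggests a mainly adult cohort. The definitions for babies are programme-wide operational definitions, so they show that the tool covers babies, not that this cohort holds many. Age is a candidate predictor and the ratios are adjusted, which helps to the extent described in step 6.

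**Conclusion.** The point holds in this form: the protocol defines its only nutritional predictor as raw BMI for all ages, the development site's card uses a different measure below 19 years, and nothing reconciles them. Following the definition as written gives LHRs and score points that do not mean the same in children and adults.

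The size is unknown and may be small. The range of 86–519 patients potentially affected rests wholly on an assumed 5–30% under 19, and the loss of the predictor at the screen rests on the assumed figures in step 5. The conclusion does not depend on any missing data or on any particular BMI threshold. It merits correction because the definition is explicit, the score is meant for bedside use without an age restriction, and the remedy is cheap.

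**What to change.** In sections 4.7.1 and 4.7.2, replace BMI with one nutritional-status variable: a Z-score category below 19 years and a BMI category from 19 years, as on the card. Name the Z-score type and the reference population. Where no Z-score was recorded, derive it from age, sex, weight and height. Calculate the crude and adjusted LHR on the combined variable, and make the same change to the variable list in the Summary.

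Report the number of patients under 19 in each cohort. Confirm that the validation site's data allow the same derivation, since only the development site's card is shown.

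The cost is a change of wording and one derived variable, from fields that the development card already holds. The downside is that Z-scores for young children will be coarse where age is held only in whole years; section 4.7.2 measures age in years, although the card allows months. Availability at the validation site remains to be checked.

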#### **Definitions of outcome variables:**

- **Death:** Death during VL treatment at the health center.
- **Cure:** Improvement in symptoms and signs of VL 20-30 days after VL treatment initiation i.e. absence of fever, decrease in spleen size, increase in haemoglobin level, weight gain and a negative test of cure (parasitological test) where indicated.
- **Transfer:** A VL patient on treatment that is sent to a higher level health facility for better management or sent to another health facility for compassionate reasons e.g. proximity of that health facility to the patients' home.
- **Defaulter:** A VL patient on treatment that absconds from treatment and does not return or returns but the VL treatment has to be restarted from the first day.
- **Treatment failure:** It is defined as a positive parasitological test at the end of VL treatment.

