#### **4.6 Exclusion Criteria**

In the derivation and external validation cohort, we will exclude all patients with the outcomes mentioned below.

1. Transferred
2. Defaulted

The transferred and defaulted patients were few (approximately 4%). Additionally in the external validation cohort, we will exclude all patients with treatment failure. There were no patients with treatment failure in the derivation cohort.

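### The score predicts death, but its comparison group is cured patients rather than survivors, so non-events are selected on what happens after admission

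*Protocol*

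**What the plan says.** Protocol section 4.4 makes the outcome death while under VL treatment at the facility. Section 4.5 then fixes the analysis set by outcome: "In the derivation and external validation cohort, we will include all patients with the outcomes mentioned below", and the two that follow are Cured and Dead. Section 4.6 excludes transferred and defaulted patients (about 4%) and adds: "Additionally in the external validation cohort, we will exclude all patients with treatment failure". For the other cohort it states: "There were no patients with treatment failure in the derivation cohort".

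The outcome definitions at the end of section 4.7.2 give five categories: death, cure, transfer, defaulter and treatment failure. Cure is improvement judged 20 to 30 days after treatment starts, spelled out as "absence of fever, decrease in spleen size, increase in haemoglobin level, weight gain and a negative test of cure (parasitological test) where indicated". Of treatment failure the Protocol says: "It is defined as a positive parasitological test at the end of VL treatment".

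Section 4.7.1 lists the admission values of spleen size, haemoglobin and BMI among the candidate predictors, along with signs such as oedema and ascites.

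**The concern.** The complement of death is survival. The plan uses a narrower group, survivors who also met a clinical definition of cure. Whether a survivor counts as a non-event therefore depends on the course after admission, and partly on change in spleen size, haemoglobin and weight, whose starting levels the score may use.

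A likelihood ratio compares how often a sign occurs in deaths with how often it occurs in the retained non-deaths. If the survivors left out differ from the others on that sign, the ratio moves. Section 4.8.2 screens variables on crude ratios (at least 2 or at most 0.5), retains them on adjusted ratios (at least 1.5 or at most 0.67) and rounds the logarithm to whole points, so a variable near a boundary can change status. In the validation cohort the same selection affects specificity and the predictive values. At admission, when the score is used, nobody knows who will later be labelled cured.

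**Working it through.** **1. Are the categories exhaustive?** Take a patient alive at the end of treatment who misses one clinical component and has no positive parasitological test.
- Dead, transferred, defaulter: no.
- Cured: no, if the listed components are all required, as the joining word suggests.
- Treatment failure: no, since that needs a positive test, and the test of cure is done only where indicated.

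Sections 4.5 and 4.6 neither include nor exclude this patient. The case can arise on the Protocol's own terms. Section 4.7.2 lets a suspected case qualify on lymphadenopathy or wasting without splenomegaly, and a spleen that is not enlarged cannot shrink.

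**2. Counts.** The plan gives no figure for such patients. From the Sample Size text:
- Derivation: 1729 − 99 = 1630 non-deaths; mortality 99/1729 = 5.73%.
- Validation: 526 − 53 = 473 non-deaths; mortality 53/526 = 10.08%.
- Validation, VL-HIV: 55 − 28 = 27 non-deaths; mortality 28/55 = 50.9%.

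Section 4.3 describes 1729 as the patients diagnosed, yet about 4% were excluded. That is 0.04 × 1729 = 69 patients if 1729 is before exclusions, or 1729/0.96 − 1729 = 72 if after. The text does not say which.

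**3. Effect on a crude likelihood ratio.** Let f be the share of all survivors lost, and r how many times as common the sign is among those lost as among all survivors. Neither is in the documents; both are assumed. With p the frequency of the sign in all survivors,

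frequency in retained survivors = p(1 − f·r)/(1 − f), so observed LHR = true LHR × (1 − f)/(1 − f·r).

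At r = 1 nothing changes. For r from 0.5 to 3, taking 1630 as the retained survivors:

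| f | Survivors lost | True 2.0 reads | True 1.5 reads | Derivation mortality with all survivors |
|---|---|---|---|---|
| 1% | 16 | 1.99–2.04 | 1.49–1.53 | 5.67% |
| 4% | 68 | 1.96–2.18 | 1.47–1.64 | 5.51% |
| 10% | 181 | 1.89–2.57 | 1.42–1.93 | 5.18% |
| 20% | 408 | 1.78–4.00 | 1.33–3.00 | 4.63% |

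Example: f = 4%, r = 3 gives 2.0 × 0.96/0.88 = 2.18. At the extreme, with p = 10% and f = 4%, a ratio of 2.0 reads 3.2 if every lost survivor has the sign and 1.92 if none has.

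**4. Effect on points.** A true ratio of 2.0 rounds to 1 point across the table (ln 1.78 = 0.58; ln 4.00 = 1.39). A true 1.5 rounds to 0 points (ln 1.5 = 0.41) but reads 1.69 at f = 10%, r = 2, and then scores 1 (ln 1.69 = 0.52). These are crude ratios; the plan takes points from adjusted ones.

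**5. Effect in validation.** Specificity over all survivors = (1 − f) × specificity in those kept + f × specificity in those lost. The shift is f times the difference between the two, in either direction, and cannot exceed f. For a fixed score and cut-off, adding survivors can only add false positives or true negatives. The plan's positive predictive value is then at or above the all-survivor value, and its negative predictive value at or below.

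If 526 is after exclusions, validation mortality with all survivors would be 9.71% (f = 4%), 9.16% (10%) or 8.23% (20%). In the VL-HIV group, if 55 is after exclusions, adding 5, 10 or 20 survivors takes 50.9% to 28/60 = 46.7%, 28/65 = 43.1% or 28/75 = 37.3%. Section 1.1 says treatment failure is more common in co-infected patients, but the number excluded is not given.

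**The case against.** The strongest reply is that the gap may be empty. The data are retrospective and exit labels already exist. The cure definition opens with general improvement in symptoms and signs, so staff may have recorded every recovered patient as cured. Section 4.6 names no unclassified survivors and reports no failures in the derivation cohort. If the exit field holds only the five categories, recoding may change nobody there. This stands as to size. The 1729 figure does not settle it, because it does not visibly account for the acknowledged 4% either.

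A reader might infer three stronger claims that the documents do not support.
- **That cure and the predictors are the same measurements.** They are not: predictors are admission values and cure uses later change. The link is selection of the comparison group.
- **That survivors did drop out.** No count or statement shows it.
- **That the score will overstate risk for patients with oedema or ascites.** Neither sign is in the cure definition; the argument assumes that such patients lose fluid and so show no weight gain. With assumed oedema in 20% of deaths and 5% of survivors, the ratio is 4.0 (1 point). Losing 25% of oedematous survivors gives 0.20/0.0380 = 5.27, ln 1.66, 2 points. But that start lies just under the rounding boundary of exp(1.5) = 4.48. From 3.0 the same loss gives 3.95, ln 1.37, still 1 point. If 20% of the other survivors were also lost, 4.0 becomes only 4.25, ln 1.45, still 1 point. A sign with no effect (5% in both groups) reads 1.95 at 50% loss, still below the screen. Direction can also reverse: losing survivors with no palpable spleen lowers the ratio for a large spleen.

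**Conclusion.** The concern holds as a defect of definition. The outcome is death, the comparison group is a post-admission clinical success, and the five categories leave a gap. The removal of surviving treatment failures from validation is explicit; the loss of other survivors is only what a literal reading would cause.

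The size is unknown. Under the assumed r of 0.5 to 3, a likelihood ratio moves by −2% to +9% at 4% of survivors lost and by −5% to +29% at 10%, which matters mainly near a threshold or rounding boundary. In the derivation cohort the effect may be nil. In the VL-HIV validation group, with only 27 non-deaths, a few excluded failures would visibly change mortality and the predictive values. The correction is worth making because it is cheap and gives the score the comparison its objective describes.

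**What to change.** - In sections 4.5 and 4.6 and the outcome definitions, define the non-event as alive at the end of VL treatment at the facility, whatever the cure status, in both cohorts. This brings surviving treatment failures back into validation. Transfers and defaulters can stay excluded as now.
- Report the number of patients in every exit category for each cohort and for the VL-HIV subset, including any survivor not labelled cured.
- State whether 1729 and 526 (and 345 and 55) are before or after exclusions.
- Keep cured-versus-dead as a sensitivity analysis, so that readers can see whether the choice matters.

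The cost is a wording change and some recoding of exit status, with no new patients. The non-event group becomes slightly larger and more mixed. Counting how many survivors missed each cure component would be informative but is not free: end-of-treatment spleen size, haemoglobin and weight are not among the section 4.7.1 study variables and would need separate extraction, so the fix does not depend on it.
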